### Outcome measures

#### Primary outcome

Time from uterine incision to delivery of baby (seconds).

#### Secondary outcomes

Maternal outcomes:

Uterine incision to closure time (minutes)Estimated blood lossNeed for blood productsVolume of blood products requiredUterine angle extensionsVisceral injury (ureter, cervix, bladder, bowel)HysterectomyGenital tract traumaMaternal admission to higher level care (HDU/ITU)Maternal deathLength of stay (nights)Post-operative wound infectionEndometritisChange in haemoglobin pre and post procedure

Neonatal outcomes:

Birth trauma (including, but not limited to, intracranial haemorrhage, skull fracture, other fracture, facial injury including bruising/facial nerve palsy, any other nerve injury)Apgar scores at 5 and 10 minNeed for resuscitationAdmission to higher level care (SBCU/NICU)Length of stay in higher level care (up to 4 weeks)Arterial cord pHHypoxic ischaemic encephalopathy (grades 1, 2 and 3)Perinatal deathNeonatal feeding

Qualitative clinician outcomes using questionnaire:

Evaluation of the Tydeman^®^ Tube and Fetal Pillow^®^ using Likert scale (acceptability, ease of use)Perception of impacted head at time of caesarean sectionPerception of ease of delivery using each deviceNeed for elevation of the fetal head using Tydeman^®^ Tube

Qualitative maternal outcomes using questionnaire:

Acceptability of Tydeman^®^ Tube and Fetal Pillow^®^

### Data handling and storage

Participants will be allocated a unique study ID number at time of recruitment, with no storage of patient identifiable information. To ensure confidentiality and data safety, all patient data will be link-anonymised at time of data entry in accordance with the Data Protection Act 2018 and UK GDPR directive. All maternal and neonatal outcome data will be collected as part of routine clinical care, including demographic and clinical data.

Data will be stored on a RedCap database. This is a secure third-party cloud provider. The database is very clear and simple to use, and predefined validation rules and data monitoring facility help to ensure accurate data entry. Access to the database will be managed by the RedCap team in collaboration with the Principal Investigator. Prospective new users must demonstrate compliance with legal, data protection and ethical guidelines before any data are released.

### Data retention and sharing

Any data relating to pregnancy care is required to be stored for at least 25 years. At the end of the study, pseudonymised research data will be locked and downloaded from the LIFT Database (on RedCap), saved in a read only format and archived according to Sponsor requirements (with Iron Mountain). Copies will also be kept on KCL Sharepoint. A file note will be placed in the Investigator Site File detailing the location of electronic data.

The consent form states that other researchers or commercial partners may wish to access anonymised data in the future. Should this be a research group outside of the trust or a commercial partner, data will be shared only according to GSTT/KCL data governance policies and where appropriate, a data agreement would be put in place when required.

### Data analysis, sample size and power calculations

Time between uterine incision and delivery of the baby reflects the degree of difficulty in disimpacting the fetal head and will be used as the primary outcome measure to compare efficacy of the devices. Estimation of usual time from uterine incision to delivery was obtained from a robust clinical database capturing all maternity statistics from our unit over a period of one year. Sample size calculation was based on an observed mean time from uterine incision to delivery of 97 s (standard deviation 94 s).

To demonstrate that the Tydeman^®^ Tube is non-inferior to the Fetal Pillow^®^, non-inferiority was defined as an increase in uterine incision to delivery time of no more than 97 s (corresponding to a doubling of mean time to 194 s). We chose doubling of the time from uterine incision to delivery as a clinically important outcome, as this would take the average time to over 3 min. A delivery time of over 3 min at caesarean section has been associated with the development of hypoxic ischaemic encephalopathy, hence exceeding this is non-desirable.

30 participants per arm provides 95% power (one-sided alpha 0.05) to determine non-inferiority. We therefore aim to recruit 30 participants to each arm as minimum. If the recruitment target is reached sooner than expected (i.e. within 3 months) then recruitment will continue up to 40 participants per arm for a maximum of 6 months. In the substudy the Tydeman^®^ Tube will only be used when an IFH is encountered unexpectedly. We do not have data to support how frequently this may occur during the study period and this will be an observational arm without pre-defined sample size.

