### Setting

The LIFT trial will be conducted at St Thomas’ Hospital, a tertiary level maternity unit in South London, UK. Neither device is currently in use at this site.

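### The 97 s non-inferiority margin is justified by a 3-minute limit that it exceeds by 14 s on the plan's own reference mean

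*Protocol article*

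**What the plan says.** All of the reasoning is in the protocol article, section Data analysis, sample size and power calculations.

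- **Reference value.** The calculation uses an "observed mean time from uterine incision to delivery of 97 s (standard deviation 94 s"), taken from one year of the unit's own records: "Estimation of usual time from uterine incision to delivery was obtained from a robust clinical database".
- **Margin.** Non-inferiority is an increase of no more than 97 s, "corresponding to a doubling of mean time to 194" s.
- **Reason for doubling.** It was chosen "as this would take the average time to over 3 min".
- **Why 3 minutes.** "A delivery time of over 3 min at caesarean section has been associated with the development of hypoxic ischaemic encephalopathy", "hence exceeding this is non-desirable".
- **Size.** 30 per arm is said to give 95% power at one-sided alpha 0.05. The Design section allows up to 40 per arm.

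The Setting section adds: "Neither device is currently in use at this site". The article gives no absolute cap on the mean and no second criterion at 3 minutes.

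**The concern.** The 3-minute value is used as a reason for the margin, but it works against it. A time difference worth detecting in a superiority trial can reasonably be one that crosses a harm threshold. A non-inferiority margin has the opposite role: it marks the largest excess that the trial will still call acceptable. If passing 3 minutes is what should be avoided, the margin has to stop there or earlier. On the plan's reference mean it stops 14 s later, so true means from 180 s to 194 s lie inside the region defined as non-inferior.

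This margin decides the primary objective, whether the Tydeman Tube is as effective as the Fetal Pillow. A positive result could come with a confidence bound that still includes a mean beyond the limit used to justify the test.

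**Working it through.** **Inputs.** From the protocol article: reference mean 97 s, SD 94 s, margin 97 s, limit 3 min = 180 s, one-sided alpha 0.05, 30 to 40 per arm. Assumed here because the article does not state them: a true difference of 0 for power, and an SD of 94 s in both arms.

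**1. The plan's own power figure.**
SE = 94 × √(2/30) = 24.27 s.
Power at margin 97 s = Φ(97/24.27 − 1.645) = Φ(2.352) = 99.1% (98.9% with the t distribution).
For 95% power, n = 2 × [(1.645 + 1.645) × 94/97]² = 20.3, so 21 per arm (22 with t).
The stated pair of 30 per arm and 95% is not reproduced, but the error is on the safe side. An unstated allowance for dropout or skewness could explain it. There is room for a tighter margin.

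**2. Where the margin falls.**
Accepted ceiling: 97 + 97 = 194 s. Excess over the limit: 194 − 180 = 14 s. Largest increase that stays at the limit: 180 − 97 = 83 s.

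**3. Chance of declaring non-inferiority under the present rule**, with the comparator mean at 97 s: Φ((97 − d)/SE − 1.645), where d is the true increase. At 40 per arm, SE = 94 × √(2/40) = 21.02 s.

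| True Tydeman Tube mean | d | 30 per arm | 40 per arm |
|---|---|---|---|
| 180 s | 83 s | Φ(0.577 − 1.645) = 14% | Φ(0.666 − 1.645) = 16% |
| 187 s | 90 s | 9% | 9% |
| 194 s | 97 s | 5% | 5% |

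With an 83 s margin the first row becomes 5% at either size.

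**4. What an observed result must look like to pass.**
At 30 per arm the observed difference must be at most 97 − 1.645 × 24.27 = 57 s, an observed mean of about 154 s if the comparator is at 97 s. At 40 per arm: 97 − 1.645 × 21.02 = 62 s, about 159 s.

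**5. Power with an 83 s margin.**
30 per arm: Φ(83/24.27 − 1.645) = Φ(1.775) = 96.2% (95.9% with t).
40 per arm: Φ(83/21.02 − 1.645) = Φ(2.304) = 98.9% (98.8% with t).
95% power needs 2 × (3.29 × 94/83)² = 27.8, so 28 per arm (29 with t).
The SD nearly equals the mean, so times are probably skewed. Simulating lognormal times with mean 97 s and SD 94 s (an assumed shape) and a Welch test gives about 94% at 30 per arm and 97% at 40.

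**6. Deliveries over 180 s**, same assumed lognormal (log SD 0.814): 12% at a mean of 97 s. At the present limit, 38% if all times double and 41% if all times shift by 97 s. At an 83 s limit, 34%.

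**The case against.** **The 14 s gap is small, and passing is unlikely near it.** It is 14/94 = 0.15 SD. A reader might infer that an arm observed to average over 3 minutes would pass. On the planning values it would not: step 4 shows that the observed mean would have to be about 154 to 159 s or less. This stands. The defect lies in what a positive result rules out.

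**The ceiling depends on an unknown comparator mean.** The 97 s is a usual-care figure from a site that uses neither device. If the Fetal Pillow mean is 83 s or less, the present margin already keeps the ceiling at or below 180 s. If it is 120 s, even an 83 s margin allows 203 s. This stands as a condition on the finding and on the fix. It does not rescue the rationale, which the protocol itself builds on 97 s.

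**The cited harm concerns single deliveries, not arm means.** This also stands. The article moves from an individual time over 3 minutes to an average over 3 minutes, so 83 s follows only if its argument is taken at the level of the mean.

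**Two tempting extensions are not supported.** A reader might attribute the whole rise from 12% to 38–41% of deliveries over 180 s, about threefold, to the misplaced margin. Most of it belongs to accepting any margin of this order: at an 83 s limit 34% remain, so the correction removes roughly 3 to 7 percentage points. A reader might also treat a ratio of 180/97 = 1.86 as interchangeable with 83 s. The two agree only at a comparator mean of 97 s (at 120 s the ceilings are 223 s and 203 s), and the ratio version has only about 90% power at 30 per arm.

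**Harm is watched by other routes.** Encephalopathy, cord pH, Apgar scores and neonatal admission are secondary outcomes, and a data monitoring committee reviews outcomes and serious adverse events. This lowers the severity but does not change what the primary test concludes.

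**Conclusion.** The point holds in a limited form. The margin and its stated reason contradict each other: on the plan's 97 s reference mean, the accepted ceiling lies 14 s beyond the limit given as its justification, and nothing else in the article caps it. The error rate at a true mean of 180 s is about 14% to 16% instead of 5%, assuming an SD of 94 s in both arms and a Fetal Pillow mean of 97 s.

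The documents do not support saying that the trial is likely to endorse a device with a mean over 3 minutes, or that any fixed difference guarantees a mean below 180 s. Should-fix, not must-fix: the gap is modest, depends on a proxy mean, and is inexpensive to close.

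**What to change.** Before comparative data are seen:

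1. Set the margin on the difference scale at no more than 83 s (180 − 97), or give a different rationale that does not place the accepted mean beyond the stated limit.
2. State that an 83 s margin keeps the Tydeman Tube mean below 180 s only if the Fetal Pillow mean is at most 97 s, and that 97 s is a usual-care figure from a site using neither device.
3. Report the proportion of deliveries over 180 s in each arm with a confidence interval, because the cited harm concerns individual deliveries.

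**Cost.** A short protocol amendment and no added patients or data; item 3 uses the times already recorded. The downside is a stricter test: at 30 per arm, power falls from the 99% that the current inputs give to about 96%, still above the stated 95%. If times are as skewed as the lognormal assumption, it is about 94% at 30 per arm and 97% at 40, a size that the protocol already allows.

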### Design

This is a prospective non-inferiority observational comparison trial with two sequential interventional arms, the first using the Fetal Pillow^®^ and the second using the Tydeman^®^ Tube. Each device has regulatory approval for routine use and therefore can be introduced into clinical practice.

At trial commencement, obstetric and midwifery staff will be trained to use the Fetal Pillow^®^ by members of the research team during dedicated training sessions. The Fetal Pillow^®^ will then be introduced into clinical practice for 3–6 months for use during all full dilatation CS, or until the recruitment target is reached (*n* = 30). The Fetal Pillow^®^ will be inserted and inflated prior to full dilatation CS, in all eligible women. Consent will be sought retrospectively, see ‘Patient Recruitment’. Once the recruitment target for the Fetal Pillow^®^ has been reached, the device will be withdrawn from clinical areas and will no longer be available for use.

Obstetric and midwifery staff will then be trained to use the Tydeman^®^ Tube and the above process repeated over a 3–6-month period, or until the recruitment target is reached (*n* = 30). For eligible women, the Tydeman^®^ Tube will be inserted prior to commencement of all full dilatation CS and will be used to elevate the fetal head if felt to be required during the caesarean by the operating surgeon.

Should recruitment be reached in a shorter time frame than expected then each arm will continue for the set time frame (3–6 months) to allow for increased data collection and loss to follow up, to a maximum of 40 women per arm.

During the Tydeman^®^ Tube arm of the study, additional Tydeman^®^ Tubes will be available for clinicians to use at their discretion for caesarean sections performed at 7–9 cm cervical dilatation as per the manufacturer’s Instructions for use, which stipulates that the Tydeman^®^ Tube can be used from 7 to 10 cm. If, during a caesarean section, the operating surgeon unexpectedly encounters an IFH they can request a Tydeman^®^ Tube to use. Consent will be sought retrospectively as per the rest of the trial. This cohort will be in addition to the recruitment target of 30 women for each device. Outcome data will be compared with an historical control group of standard practice (using no device).

Recruited participants and clinicians involved in device use will be asked to complete a questionnaire regarding their views of the device.

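### The stated 95% power with 30 per arm is not the power of the written 97-s margin, which is about 99%; the assumption or scale behind the 95% is not stated

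*Protocol article*

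**What the plan says.** The primary outcome is given in raw units: "Time from uterine incision to delivery of baby (seconds") (Protocol article, Primary outcome). The section on data analysis, sample size and power bases the calculation on an "observed mean time from uterine incision to delivery of 97 s (standard deviation 94 s"), taken from one year of the unit's own records. In the same section "non-inferiority was defined as an increase in uterine incision to delivery time of no more than 97 s", with the gloss "corresponding to a doubling of mean time to 194 s". The size follows: "30 participants per arm provides 95% power (one-sided alpha 0.05) to determine non-inferiority", and "We therefore aim to recruit 30 participants to each arm as minimum". Loss to follow-up appears only in the Design section, where recruitment may run on "to allow for increased data collection and loss to follow up, to a maximum of 40 women per arm". The article names no log transformation or ratio analysis, and gives neither an assumed true difference nor an attrition rate.

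**The concern.** A margin slightly larger than one SD, with 30 per arm, should give power well above 95%. If the stated power does not follow from the stated margin, SD and alpha, then either the figure is wrong or it was computed for something other than what is written.

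The second possibility matters because the article describes the margin in two ways, as an absolute 97 s and as a doubling. These are different criteria unless the comparator mean is 97 s. That figure is the unit's usual time, and the Setting section says that neither device is currently in use there, so the Fetal Pillow mean may well differ from it. If the scale is left open, it could be settled after the data are seen, in an open study with sequential arms and about 60 women.

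**Working it through.** **Inputs** (Protocol article, section on data analysis, sample size and power): SD 94 s, mean 97 s, margin 97 s, one-sided alpha 0.05, 30 per arm. The true difference is not stated; I take it as 0.

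**1. Power of the written criterion.**
- SE = 94 × √(2/30) = 24.27 s.
- Power = Φ(97/24.27 − 1.645) = Φ(2.352) = 99.1%; by noncentral t, 98.9%.
- n per arm for 95% = 2 × (94/97)² × (1.645 + 1.645)² = 20.3, so 21.
- Skewed times with mean 97 s and SD 94 s, no true difference, t-test of the 97-s margin at n = 30 (simulated): 97.2% with lognormal times, 98.3% with gamma times.

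The stated 95% is not reproduced.

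**2. Other readings with the stated inputs unchanged.**
- Two-sided alpha 0.05: 97.9%, and 25 per arm for 95%.
- Two one-sided tests at 0.05: 98.1%.
- Log scale, ratio margin 2: SD of log time = √ln(1 + (94/97)²) = 0.814. n = 2 × (0.814/ln 2)² × 3.29² = 29.8, so 30. Power at 30 = Φ(ln 2/(0.814 × √(2/30)) − 1.645) = Φ(3.299 − 1.645) = 95.1%; by noncentral t, 94.7%.

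Of the standard variants tried, only the log-scale ratio gives both 30 and 95% without changing or adding an input.

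**3. Readings that keep the 97-s criterion and change or add an input.**
- True difference of 17 s: Φ((97 − 17)/24.27 − 1.645) = 95.1%.
- 30% attrition: 21/0.7 = 30 recruited; 21 analysed per arm gives 95.5%.
- SD of about 114 s in both arms: 95%.

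**4. When the two descriptions of the margin agree.** With Fetal Pillow mean M, the absolute margin allows M + 97 and a doubling allows 2M. They are equal only at M = 97. The other values of M below are illustrative assumptions; the article gives no mean time with the device.

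| M (s) | M + 97 (s) | 2M (s) | (M + 97)/M |
|---|---|---|---|
| 60 | 157 | 120 | 2.6 |
| 97 | 194 | 194 | 2.0 |
| 130 | 227 | 260 | 1.7 |

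**5. What a log-scale criterion would test.** Under the lognormal model the geometric mean is 97/√(1 + (94/97)²) = 69.7 s, and twice that is 139 s. With gamma times of the same mean and SD, the log-scale test at n = 30 has about 70% power, so its 95% depends on the lognormal shape.

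**The case against.** The strongest defence is that the article condenses a fuller protocol. An assumed true difference or an attrition allowance may stand there, and either would bring the power of the written criterion to about 95%. This stands as a limit on the explanation: a reader might infer that the trial was in fact powered on a ratio and that the written criterion is therefore not the one used. The match is close, but nothing in the article says so, and it is not the only route to 95%. The defence does not rescue the sentence as printed, because the inputs given with it lead to about 99%. The one mention of loss to follow-up is also tied to the extension to 40, not to the 30.

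It can also be said that the error is harmless in direction. That is right for the written criterion: 30 per arm is more than enough, even with lognormal skew, and no patient number or margin has to change.

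A reader might further infer that skew breaks the error rate of a test of the 97-s margin. At a true doubling of lognormal times, a Welch test wrongly declares non-inferiority about 9% of the time. But that case needs the Tydeman Tube SD to double as well, to 188 s. With the only SD that the article gives, 94 s, the rate at a true increase of 97 s is about 4% to 5%. The documents do not support the unconditional claim, and the choice of test is commonly left to the SAP.

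Nor do they support moving the primary criterion to a geometric-mean ratio as the default repair. The article justifies the margin by the average time passing 3 minutes, which is an argument about the arithmetic mean in seconds. Doubling the geometric mean gives 139 s, below 3 minutes.

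**Conclusion.** The point holds as a misstatement of power and an unstated assumption. For the written criterion the power is about 99% (about 97% with lognormal times), against 95% stated; 21 per arm, not 30, would give 95%. This rests on the article's SD, margin and alpha, an SD of 94 s in both arms, and no true difference. The error is conservative, so it does not weaken the trial's ability to meet its written criterion.

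That the calculation was done for a log-scale ratio of 2 is likely but undocumented. The practical reason to act is that the two descriptions of the margin separate as soon as the Fetal Pillow mean is not 97 s. The article should therefore leave no doubt which of them decides the primary result.

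**What to change.** In the section on data analysis, sample size and power:

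1. Keep the difference in mean times with the 97-s margin. Either restate the power for 30 per arm as about 99% (about 97% under lognormal skew), or state the true difference, attrition or other assumption that yields 95%.
2. State before the analysis that the margin is the absolute 97 s whatever the observed Fetal Pillow mean, and that the doubling only describes how it was derived from the unit's usual figure.
3. If a ratio of 2 on the log scale was in fact powered, say so and define the criterion on that scale. Add that it then concerns geometric means, that its link to the 3-minute rationale has to be argued afresh, and that the 95% depends on lognormal times (about 70% with gamma times).

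The cost is rewording one section, by amendment if the full protocol carries the same text. No extra patients are needed.

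### On the plan's own inputs, 30 per arm gives about 98% power at one-sided 0.025, so one-sided 0.05 is not needed to reach the stated 95%

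*Protocol article*

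**What the plan says.** All the figures are in the protocol article, under Data analysis, sample size and power calculations. A year of unit data gave a mean incision-to-delivery time of 97 s with an SD of 94 s. The margin is set equal to that mean: "non-inferiority was defined as an increase in uterine incision to delivery time of no more than 97 s". The power statement is "30 participants per arm provides 95% power (one-sided alpha 0.05) to determine non-inferiority", followed by "We therefore aim to recruit 30 participants to each arm as minimum". If the target is met early, "recruitment will continue up to 40 participants per arm for a maximum of 6 months". The Design section gives the purpose of the extra women: "to allow for increased data collection and loss to follow up, to a maximum of 40 women per arm".

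The article states no true difference between devices, no dropout rate and no reason for choosing one-sided 0.05. The Design section describes a "prospective non-inferiority observational comparison trial with two sequential interventional arms", so the arms are not randomised.

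**The concern.** A looser alpha in a small single-site study is usually defended on feasibility: the stricter level would need more women than can be recruited. The printed figures do not support that defence here, because the planned 30 per arm already exceeds the stated power at 0.025.

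The error that alpha controls is a claim of non-inferiority for a Tube whose mean time is really at the margin, 97 + 97 = 194 s. The protocol itself links times over 3 minutes to hypoxic ischaemic encephalopathy and regards them as undesirable. At one-sided 0.05 the nominal chance of that error is 5%; at 0.025 it is 2.5%.

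**Working it through.** **Inputs.** SD 94 s, margin 97 s, 30 per arm, one-sided alpha 0.05 and stated power 95%, all from the sample size section. The true difference is not stated and is taken as 0 s. No dropout rate is stated; the allowance is made by going above 30, so 30 is taken as the number analysed.

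**1. The plan's own figure.**
- SE of the difference = 94 × √(2/30) = 24.27 s; 97 / 24.27 = 4.00.
- Normal approximation at 0.05: Φ(4.00 − 1.645) = 99.1%.
- Noncentral t, 58 df: 98.9%.
- n per arm for 95% power = 2 × [94 × (1.645 + 1.645) / 97]² = 20.3, so 21 (22 by t).

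The stated 95% is not reproduced; the printed inputs give about 99%. By the normal approximation it would be exact with an SD of about 114 s or a true Tube excess of about 17 s. Neither is stated.

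**2. The same design at one-sided 0.025.**
- Normal: Φ(4.00 − 1.96) = 97.9%. Noncentral t: 97.6%.
- n per arm for 95% power = 2 × [94 × (1.960 + 1.645) / 97]² = 24.4, so 25 (26 by t).

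The cost against 0.05 is 98.9 − 97.6 = 1.3 points on rounded figures (98.94 − 97.56 = 1.4 unrounded).

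**3. Largest observed excess that still passes** (observed SD 94 s): 97 − t × 24.27.
- At 0.05: 97 − 1.672 × 24.27 = 56.4 s.
- At 0.025: 97 − 2.002 × 24.27 = 48.4 s.

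**4. How far the power holds if the Tube is truly slower** (noncentral t, SD 94 s).

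| True excess | n per arm | 0.05 | 0.025 |
|---|---|---|---|
| 0 s | 30 | 98.9% | 97.6% |
| 5 s | 30 | 98.2% | 96.1% |
| 10 s | 30 | 97.1% | 94.1% |
| 20 s | 30 | 93.2% | 87.7% |
| 10 s | 40 | 99.3% | 98.3% |

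At 0.025 and 30 per arm, 95% is kept up to a true excess of about 8 s.

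**5. Skewed times.** A positive time with mean 97 s and SD 94 s is probably right-skewed. The shape is not given, so lognormal is an assumption (Welch test, 200,000 simulated trials).

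| True excess, SD 94 s in both arms | n per arm | 0.05 | 0.025 |
|---|---|---|---|
| 0 s | 30 | 97.2% | 95.2% |
| 5 s | 30 | 96.4% | 94.0% |
| 5 s | 40 | 98.6% | 97.5% |

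If the Tube SD rises in proportion to its mean, the 5 s row at 30 per arm becomes 95.6% and 92.9%, and at 40 per arm 98.1% and 96.6%.

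**6. False non-inferiority at the margin** (Tube mean 194 s, lognormal, 30 per arm).
- Tube SD still 94 s: about 4.2% at 0.05 and 1.9% at 0.025.
- Tube SD assumed to double to 188 s: about 9.0% and 5.5% to 5.6%.

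**The case against.** The strongest reply is that nothing here is misstated about alpha. The level is fixed in advance and disclosed, no other part of the protocol sets 0.025 as the standard, and a one-sided 0.05 can be defended in an observational comparison of two devices that already have regulatory approval. That stands: this is an improvement to a choice, not the correction of an error.

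A second reply is that the trade-off is real. A reader might infer from the zero-difference figures that the looser level gains nothing and that tightening it is free. The documents do not support that. It holds only against the 95% target, with no true difference and an SD of 94 s. With lognormal times and a 5 s true excess, 30 per arm keeps 95% at 0.05 and loses it at 0.025. If the stated 95% rests on an unstated 17 s excess or an SD of 114 s, power at 0.025 is about 90% to 91%. This stands and limits how the fix may be worded.

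A reader might also infer that skew alone makes one-sided 0.05 more permissive than it looks. With equal SDs the simulated rate is below nominal. The 9.0% figure needs the further assumption that the Tube SD doubles, which the protocol does not state, and in that scenario 0.025 also exceeds its nominal level.

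Finally, neither alpha controls bias from sequential, non-randomised arms, and how far a mean of 194 s is acceptable is a question about the margin. Both are correct and separate from this point.

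**Conclusion.** The point holds in a limited form. On the printed inputs, 30 per arm gives about 99% power at one-sided 0.05 and about 98% at 0.025, so the looser level is not needed to reach the stated 95%, and the 95% itself does not follow from those inputs. Moving to 0.025 halves the nominal risk of a false non-inferiority claim and lowers the largest passing observed excess from about 56 s to about 48 s.

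This rests on an SD of 94 s, no true difference and 30 women analysed per arm. The margin for departure is modest: about 8 s of true excess under the t test, and less than 5 s if times are lognormal. The claim at issue is non-inferiority; the design gives no basis for reading a pass as equivalence. The change is a cheap improvement that should be made, not a repair of a faulty calculation of alpha.

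**What to change.** In the sample size section of the protocol:
- Set one-sided alpha to 0.025.
- State that non-inferiority is concluded only if the upper limit of the two-sided 95% interval for the mean difference (Tube minus Pillow) is below the margin.
- Restate power as about 98% at 30 per arm, assuming SD 94 s and no true difference.
- If the 95% was calculated with a true difference or a larger SD, state that input and recompute power at 0.025 from it.

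The cost is a line or two of text and about 1.4 points of power (about 97% to 95% with lognormal times). Power at 30 per arm falls below 95% if the Tube is truly about 10 s slower (t test) or about 5 s slower (lognormal). Forty per arm covers both cases, at about 98% and 97%. That ceiling is already in the plan, but it is reached only if recruitment is fast enough and is also meant to absorb loss to follow-up, so it should not be treated as guaranteed. The change should be made before any outcome data are compared between arms.
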